#### **Sub-Study Aims (exploratory):**

The *GoKids* intervention group will show greater improvement in CVD risk measurements, including vascular reactivity, fasting lipid and glucose metabolism parameters, resting energy expenditure, left ventricular hypertrophy, and inflammatory measures compared to the *Advice-Only* condition.

**Primary Endpoint:** change in insulin resistance as measured by HOMA-IR.

### b. Background and Rationale

Obesity is increasingly common in childhood and adolescence, and is a major threat to health. Childhood obesity is predictive of risk for chronic conditions, including type 2 diabetes and cardiovascular disease (CVD) in adulthood (Morrison 2008), and obese pediatric patients have high rates of cardiovascular risk factors during childhood. Declining levels of physical fitness among children and adolescents contribute to the obesity-associated health risks of future generations (American Heart Association 2005). Physical activity is known to have physiologic benefits in many areas; recommendations to increase physical activity levels in children are evidence-based (Strong 2005).

Exercise training is a type of physical activity that can improve physical fitness. Exercise training improves a host of physiological risk factors and provides psychosocial benefits for children who are at increased CVD risk, including those with obesity (Klijn 2007) and diabetes (Caranti 2007). Furthermore, several recent pediatric studies suggest that exercise training reduces cardiometabolic risk factors (Ferguson 1999) and the intra-individual clustering of cardiometabolic risk factors (Reinehr 2009). Reduction in risk factors may occur both by direct effects (e.g. blood pressure reduction, increasing HDL), and indirectly through weight reduction. Despite evidence of its benefits, exercise training prescribed by physicians for overweight children is traditionally vague, developmentally inappropriate, and/or fraught with psychological financial & practical barriers. Recommendations may not be supported by sufficient motivational assistance.

Recently there has been increased interest in the use of interactive and new technologies to promote physical activity, prevent or reverse unhealthy weight, and improve physical fitness in youth ([name] 2007; An (in press); Daley 2009). These technologies include popular video games that feature player movement, physiologic monitoring devices (e.g., pedometers and heart rate monitors), and internet mediated counseling. Initial studies in adults demonstrate that interactive technologies can intensify antismoking attitudes, improve prevention behaviors, influence dietary habits, increase physical activity, strengthen adherence to medical treatment plans, or improve chronic disease self-management (Norman 2007). The few published pediatric studies of exer-gaming include design limitations such as: 1) small sample sizes; 2) inadequate measures of physical activity and body composition (Trost 2008), and 3) an absence of the use of evidence-based behavioral strategies, important components of interventions designed to increase and sustain physical activity ([name] 2006). Published exercise studies have not included children at increased CVD risk. “Exer-gaming” techniques should be tested in pediatric patients with CVD risk factors to determine if they increase physical activity, and whether this increases physical fitness, decreases body fat, and reduces CVD risk factors.

### c. Timeline

**2010**

| Study Event | Jan | Feb | Mar | Apr | May | Jun | Jul | Aug | Sep | Oct | Nov | Dec |
|-------------|-----|-----|-----|-----|-----|-----|-----|-----|-----|-----|-----|-----|
| Recruitment |     | X   |     |     |     | X   |     |     | X   |     |     |     |
| Consent     |     | X   |     |     |     | X   |     |     | X   |     |     |     |
| Screening   |     | X   |     |     |     | X   |     |     | X   |     |     |     |
| Baseline    |     |     | X   |     |     |     |     |     | X   |     |     |     |
| Randomize   |     |     | X   |     |     |     |     |     | X   |     |     |     |

|                                       |  |  |   |   |   |   |  |  |   |   |   |   |
|---------------------------------------|--|--|---|---|---|---|--|--|---|---|---|---|
| Intervention and Advice-Only sessions |  |  | X | X | X |   |  |  | X | X | X |   |
| 12-week assessment                    |  |  |   |   |   | X |  |  |   |   |   | X |

### III. Recruitment

#### a. Inclusion and Exclusion Criteria

##### Main Experiment

###### Inclusion criteria

- enrolled in grades 3-5
- able to attend GoKids and school-based weekly educational sessions for 12 weeks and complete baseline and follow-up testing
- informed consent from a parent or legal guardian and written assent from the child
- English speaking child
- free from medical conditions that would prohibit exercise as indicated by permission to participate in school physical education, and by review of screening questions with clearance from primary care provider as necessary

###### Exclusion criteria

- abnormalities on screening/baseline evaluation that could pose a significant risk for exercise
- illness that would limit participation
- plans to move out of the area or change schools in the next 6 months

##### Sub-Study

###### Inclusion criteria

- participation in the Main Experiment
- able to attend CHB CTSU for two ~2 hour visits occurring at baseline and follow-up
- informed consent for the Sub-Study from a parent or legal guardian and written assent (from the child)
- HDL <50 mg/dL, TC > 170 mg/dL, blood pressures > 90th percentile for age, gender and height, OR waist circumference > 90th percentile (NHANES)

###### Exclusion criteria

- as above

#### b. Recruitment Procedures

##### Main Experiment

Children will be recruited from Boston Public Schools. [name], the principal of Russell Elementary School has expressed interest in participation and will be instrumental in

guiding recruitment logistics. Recruitment materials briefly describing the Main Experiment and the Sub-Study will be sent home with school children along with a consent form and the screening form. Teachers designated by the principal may contact parents to follow-up regarding enrollment materials. If health concerns are raised by the screening form, physician clearance will be requested from the primary care physician. The child assent form will be completed during his or her first visit to GoKids. Students from the third through fifth grades will be approached to participate. Study activity will occur outside school hours, unless otherwise requested by school officials.

#### **Sub-study**

After the baseline assessment for the Main Experiment, eligibility for participation in the Sub-Study will be reviewed. Parents will be contacted by phone to receive Main Experiment lab results; at this time, if the child meets the eligibility criteria for the Sub-Study, the parent and child will be invited to join the Sub-Study. If the family is amenable, a CHB CTSU visit will be arranged prior to the start of physical activity. Consent and assent for the Sub-Study will be collected at the time of the CTSU visit.

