#### **e. Baseline Assessment**

##### **Main Experiment**

All participants will be asked to attend GoKids UMass Boston (Boston, MA) for baseline measurements. During the baseline visit, research personnel will screen for eligibility and obtain a comprehensive assessment of baseline cardiovascular, physical activity, and psychosocial measures under the supervision of trained research personnel and exercise physiologists. Non-fasting finger stick total cholesterol (TC) and high-density lipoprotein (HDL) testing will be offered. If no exclusionary criteria become apparent during baseline measurements, participants will be individually randomized to either the center-based exercise intervention (*GoKids*) or an *Advice-Only* condition for 12 weeks, with a follow-up evaluation at 12 weeks after baseline. See Study Measurements and Data Collection for more information.

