##### **Sub-study**

All eligible participants will be scheduled for a sub-study visit in the CHB CTSU for baseline measurements. During the baseline visit, research personnel will obtain informed consent and assent for participation in the sub-study. Once consent/assent is obtained, research personnel will complete baseline measurements under the supervision of the sub-study PI. See Study Measurements and Data Collection for more information.

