### b. Intervention Protocol

Following the baseline measurements, participants will be individually randomized into one of the following two treatment conditions: *GoKids* and *Advice-Only*. All participants will receive weekly group nutrition and activity education sessions lasting approximately 30 minutes supported by printed dietary, exercise and motivational advice adapted from existing materials (clinic materials, AHA, CDC and NHLBI materials). The sessions will be taught by UMass student educators trained to deliver a standard message. The *Advice-Only* intervention will consist entirely of these weekly sessions. It was felt to be unethical to offer no support for following a heart-healthy lifestyle to children randomized to the *Advice-Only* condition given the high rate of overweight/obesity and generally poor diet and activity levels in our study population. The *Advice-Only* group will be offered the 12-week GoKids physical activity experience at the close of the trial as an incentive for participation. Children in both groups will receive a small incentive during week 6 and then at the close of the intervention. In addition, classroom and school-wide incentives will be offered, such as healthy lifestyle education sessions for other classes; details will be discussed with the school principal.

The *GoKids* group will receive the GoKids integrated program which uses theory-based behavioral strategies and center-based exercise training. It includes an initial exercise consultation, orientation, and tri-weekly training at *GoKids* Boston. Previous research from GoKids Boston indicates that the energy expenditure from playing interactive video games is comparable to what is expended while walking on a treadmill for the same amount of time. In addition, the use of interactive video games is at a sufficient intensity to engage the participant in MVPA (Bailey et al., 2008). Exercise sessions in the *GoKids* condition will occur 3 times per week lasting 60 minutes each session, for 12-weeks and will include a variety of exercise training activities using the latest interactive exercise games, treadmills, elliptical machines, and strength training equipment located at the UMass facility. All sessions will be supervised by a trained exercise physiologist, with nurse practitioner support available and the classroom teacher present and active with the students.

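### The sub-study visit is tied to the start of physical activity instead of release of the allocation, so sub-study entry and baseline timing may depend on arm

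*Protocol*

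**What the plan says.** **Randomization.** Section III.e (Main Experiment) describes the baseline visit at the GoKids site and continues: "If no exclusionary criteria become apparent during baseline measurements, participants will be individually randomized". Section IV.b puts it as "Following the baseline measurements, participants will be individually randomized into one of the following two treatment conditions". Section IV.c adds that assignment comes once eligibility is confirmed, and that the PI is blind to assignment and block sizes.

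**Sub-study entry.** Section III.b (Sub-study) starts from the same point: "After the baseline assessment for the Main Experiment, eligibility for participation in the Sub-Study will be reviewed". Parents are then phoned with the Main Experiment laboratory results and, if the child qualifies, invited. For those who agree, "a CHB CTSU visit will be arranged prior to the start of physical activity". Consent comes at that visit: "Consent and assent for the Sub-Study will be collected at the time of the CTSU visit". Section III.e (Sub-study) repeats this order: "Once consent/assent is obtained, research personnel will complete baseline measurements under the supervision of the sub-study PI".

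**Arms.** Section IV.b says the Advice-Only "intervention will consist entirely of these weekly sessions". The GoKids activity programme is offered to that arm only when the trial closes.

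**Endpoint.** The sub-study aims in section I.a are headed exploratory. Their primary endpoint is "change in insulin resistance as measured by HOMA-IR", and the aim is worded as a comparison of GoKids with Advice-Only.

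**The concern.** Randomizing the main trial makes the arms comparable within the sub-study only if joining it cannot depend on the arm. Here a separate decision, taken after a phone call and at a hospital visit, may fall after allocation. A family allocated to education alone may be less willing, or more willing, to attend two hospital visits of about two hours each than a family allocated to the exercise programme. If willingness also relates to how HOMA-IR changes, the two sub-study groups differ for reasons other than the intervention. The same applies to the vascular, fasting lipid and other sub-study measures. Analysis cannot reliably repair selection on unmeasured motivation.

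Baseline timing is a second issue. GoKids children must be tested before their exercise begins. Advice-Only children have no study exercise to mark that point, so their fasting baseline could be drawn after education sessions have started.

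**Working it through.** The plan states no figure to reproduce. The check concerns the order of events, followed by an illustration of possible size.

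**Order of events**

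| Event | Must follow | Must precede | Where |
|---|---|---|---|
| Randomization | Main Experiment baseline, eligibility confirmed | not stated | III.e, IV.b, IV.c |
| Sub-study eligibility review and phone invitation | Main Experiment baseline | CTSU visit | III.b |
| CTSU visit: consent, then baseline tests | phone invitation | start of physical activity | III.b, III.e |
| Exercise sessions (GoKids arm only) | randomization | not applicable | IV.b |

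1. Randomization and the sub-study steps both start from the Main Experiment baseline. No section orders one against the other.
2. The single event that limits the CTSU visit, the start of physical activity, itself comes after randomization. Meeting that limit does not place consent before allocation.
3. The weekly schedule in IV.b shows no exercise for Advice-Only, so the limit has no clear referent there.
4. The calendar does not settle the order. Sub-study baseline is in March or September (IV.a), and randomization and the first sessions fall in those same months (I.c).
5. Stated blinding covers the PI only. Nothing withholds the arm from families or from the study coordinator, who may take sub-study consent (III.d).

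A site could therefore follow the text exactly and still randomize a child, tell the family, and then invite them.

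**Illustration of size.** Only the 50 children per arm (IV.c) comes from the document. Assumed inputs:
- 30% to 70% of children qualify for the sub-study.
- Families join when a standard-normal willingness score exceeds a threshold that depends on arm.
- The correlation ρ between that score and change in HOMA-IR is 0.2 to 0.4.

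Mean willingness among joiners at uptake p is m(p) = φ(z)/p, where z is the upper-p point of the normal distribution. This gives m(0.80) = 0.350, m(0.70) = 0.497, m(0.50) = 0.798 and m(0.40) = 0.966.

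Bias in SD units = ρ × [m(p Advice-Only) − m(p GoKids)].

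Type I error at two-sided 5% = Φ(−1.96 + b/SE) + Φ(−1.96 − b/SE), where b is the bias, SE = √(1/n₁ + 1/n₂) and n = 50 × share eligible × uptake.

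Worked case: 50% eligible, uptake 70% against 50%, ρ = 0.4.
- n = 50 × 0.5 × 0.7 = 17.5 and 50 × 0.5 × 0.5 = 12.5.
- Bias = 0.4 × (0.798 − 0.497) = 0.12 SD.
- SE = √(1/17.5 + 1/12.5) = 0.370.
- Type I error = 0.062.

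| Uptake, GoKids v Advice-Only | Bias (SD) | Type I error |
|---|---|---|
| 60% v 60% | 0 | 0.050 |
| 70% v 50% | 0.06 to 0.12 | 0.052 to 0.067 |
| 80% v 50% | 0.09 to 0.18 | 0.054 to 0.090 |
| 80% v 40% | 0.12 to 0.25 | 0.057 to 0.117 |

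The direction depends on which arm has the lower uptake and on the sign of ρ, neither of which is known.

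**The case against.** A reader might infer that Advice-Only children have no timing limit at all. The documents do not support that: IV.a gives a baseline month, March or September, for every sub-study child. The physical-activity phrase is also worded for all invited families, and I.c shows both arms' sessions on one shared row. It can therefore be read as a common programme start date. On that reading the difference in baseline timing shrinks, but consent may still follow allocation.

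A reader might also infer that families are told their arm before they decide, and that the HOMA-IR comparison is broken. Neither is stated. The phone call is described as giving results and an invitation, and no section says when the arm is disclosed. The wording in IV.b, "Following the baseline measurements, participants will be individually randomized into one of the following two treatment conditions", could be stretched to include the CTSU baseline, since III.e calls those tests baseline measurements too. Bias also needs three things together: disclosure before consent, uptake that differs by arm, and a link between willingness and outcome. The document establishes none of them.

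The timing effect is limited as well. Both arms receive the same 30-minute weekly education, and a late draw within the baseline month would follow only a few sessions. The aim is exploratory, in what IV.c calls a pilot.

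All of this stands and limits the point to exposure. It does not remove the gap: no section requires sub-study consent and baseline before allocation is made or released, and the one explicit anchor does not do so.

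**Conclusion.** The point holds as a badly chosen anchor. The protocol permits, but does not prescribe, arm-dependent entry to the sub-study and unequal baseline timing. The only limit besides the physical-activity anchor is a month that also contains randomization and the first sessions.

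The size cannot be estimated from the document. The illustrated biases of 0.06 to 0.25 SD rest wholly on assumed uptake and correlation, and the type I error figures also on assumed eligibility. With a 70% against 50% split the effect on type I error is modest. With uptake independent of arm there is no bias.

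The exposure is confined to the exploratory sub-study comparisons, HOMA-IR first among them. The primary MVPA comparison is untouched. The change is worth making because it is cheap and the selection could not be reliably undone in analysis.

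**What to change.** In III.b and IV.c, replace the physical-activity anchor with release of the allocation. Suggested wording: *For children eligible for the sub-study, the CTSU consent and baseline tests are completed, or the invitation is declined, before the allocation is made or released. The same window applies in both arms. Families not reached, or not attending, by a fixed date before the cohort's sessions begin count as not enrolled in the sub-study, and the allocation is then released.*

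The cut-off date is needed because otherwise a family that cannot be reached, or that accepts and does not attend, would hold up its child's allocation indefinitely. Bring both parts of III.e and the randomization sentence in IV.b into line with this order.

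The sub-study criteria (HDL, total cholesterol, blood pressure, waist circumference) are all measured at the Main Experiment baseline, so eligible children can be identified before allocation. The hospital group already runs both randomization and the sub-study, and no procedure is added. The cost is a short, bounded hold on allocation for eligible children, whose length the document gives no basis to state, and possibly a few lost sub-study participants.

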### **c. Screening**

#### **Main Experiment**

Prior to participation in screening, enrollment forms filled out by parents either at evening sessions at the school or at home will be required. If risks for exercise are discovered on the enrollment form, physician clearance for participation will be required. Study staff will help facilitate this by faxing forms to pediatricians and coordinating the return of these forms.

#### **Sub-study**

After the baseline assessment for the Main Experiment, eligibility for participation in the Sub-Study will be reviewed (see Recruitment Procedures, above).

### **d. Informed Consent**

#### **Main Experiment**

Informed consent will be obtained by mailing enrollment packets home to parents prior to conducting baseline procedures. Parents may directly contact study staff with any questions regarding information in the consent form.

Assent will be obtained by the study coordinator or PIs prior to conducting baseline procedures at GoKids. The PI or study coordinator will verbally review the assent form, will discuss the study and answer any questions. The child will be instructed that participation is voluntary and that s/he is free to withdraw at anytime.

#### **Sub-study**

Informed consent and assent will be obtained by the study coordinator or PIs prior to conducting baseline procedures in the CHB CTSU. The parent or legal guardian or adult participant will be given the consent form to read and a verbal explanation of the study risks and benefits of participation will be provided by the study coordinator or PIs. The PIs will be available to review the study, clarify any areas that are confusing, and answer any questions. The purpose, study duration, procedures, potential risks and benefits, and the subjects' rights will be explained. The subject will be instructed that participation is voluntary, and that his or her medical care or participation in the Main Experiment will not be affected by his or her participation and that s/he is free to withdraw at any time. Asking the subject and parent or legal guardian to explain the study in his/her own words will assess the subject's understanding and autonomy. Each subject will be informed that, if he/she is a CHB patient, access to his/her medical records and trial related

source documents will be granted for research-related monitoring and IRB review, and regulatory inspection. Subjects also will be informed that if abnormal test results are obtained during the screening process that could affect the care they receive from their primary care physician, their tests results will be provided to their physician with patient/parent permission.

#### **e. Baseline Assessment**

##### **Main Experiment**

All participants will be asked to attend GoKids UMass Boston (Boston, MA) for baseline measurements. During the baseline visit, research personnel will screen for eligibility and obtain a comprehensive assessment of baseline cardiovascular, physical activity, and psychosocial measures under the supervision of trained research personnel and exercise physiologists. Non-fasting finger stick total cholesterol (TC) and high-density lipoprotein (HDL) testing will be offered. If no exclusionary criteria become apparent during baseline measurements, participants will be individually randomized to either the center-based exercise intervention (*GoKids*) or an *Advice-Only* condition for 12 weeks, with a follow-up evaluation at 12 weeks after baseline. See Study Measurements and Data Collection for more information.

